### Procedures

As depicted in Fig. 1, our study will comprise a 12-week study period that starts and ends with study visits for baseline and follow-up examinations. At study visit 1, participants will be allocated to the study groups according to randomization after informed consent is given. Blood glucose meters from all participants will be read out. Participants of the interventional group will download both the mySugr PRO application (mySugr GmbH, Austria) and the application for mobile EMA capturing time-varying real-life experience (mEMA, ilumivu, USA). Applications will be used via pseudonymized study accounts. Baseline examination at visit 1 will then involve the collection of blood glucose data and the completion of questionnaires on patient-reported outcomes (PRO, see below). Blood glucose data comprise the self-monitored average glucose levels, the corresponding percentages of hypoglycemic (< 70 mg/dl; < 54 mg/dl), euglycemic (70–180 mg/dl), and hyperglycemic (> 180 mg/dl) values, as well as the last documented or routinely assessed HbA1c. During the 12-week study period, participants of the interventional group will use mySugr PRO for diabetes self-management, while control patients will continue with their present mode of self-management. Additionally, participants of the interventional group will daily report their real-world experience via mEMA, both at the beginning and at the end of the interventional phase over a period of 10 days each. Follow-up examination at visit 2 will assess the same data as the baseline evaluation at visit 1, extended by an additional questionnaire on the perceived quality of the intervention and treatment satisfaction (interventional group). Adverse events and serious adverse events will be documented throughout the study. There will be no provisions for ancillary and post-trial care, and there will be no post-trial compensation since we expect no harm due to trial participation.

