### Study population

People diagnosed with type 1 diabetes (ICD-10 code E10), type 2 diabetes (ICD-10 code E11), or gestational diabetes (ICD-10 code O24.4) are eligible for this study. The inclusion criteria further comprise the capability for both daily blood glucose measurements and corresponding adjustment of therapy, age ≥ 16 years, last obtained HbA1c value < 12% (107.6 mmol/mol), possession of a smartphone compatible with the intervention (Android ≥ 5.0; iOS ≥ 11.4), willingness to accept terms of conditions of the app, German language skills, and provision of informed consent. Patients will be excluded if they are currently using continuous glucose monitoring (CGM) systems (real-time and intermittently scanned CGM), if they used digital diabetes diaries or digital applications for therapy documentation in the last 3 months before study entry, if they have any medical conditions contradicting with diabetes therapy and study participation, or if they are simultaneously participating in another clinical trial.

For the primary outcome, the calculation of the intended sample size was based on the assumption of an expected effect size of 0.3 standard deviations. Statistically, this assumption was derived from a previous analysis evaluating the effect of the digital health application on diabetes distress [27]. Clinically, this effect size was chosen to allow interpretation of clinically meaningful effects as effect sizes below 0.3 have limited implications for clinical practice. Employing a 2:1 randomization, power analysis revealed that 396 participants would be required to achieve a power of 1 − *β* = 0.80 with a two-sided *α* error of 0.05. With an assumed drop-out rate of 15%, we intend to recruit 466 participants (311 intervention, 155 control). Drop-out will be defined as participants who completed baseline assessment of the primary endpoint but were lost to follow-up or withdrew informed consent.

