### Statistical analysis

All evaluations on positive care effects will base on intention-to-treat analyses. Missing values will be identified and replaced by using multiple imputation [40]. Additional sensitivity analysis will be performed with the per-protocol population. Descriptive data will be presented as absolute and relative frequencies (categorical, nominal data), median and interquartile range (75% percentile and 25% percentile; ordinal data), and mean ± SD (interval-scaled variables). The differences between the interventional and control groups will be assessed by the analysis of covariance with baseline data as a covariate, and follow-up data and group membership as dependent and independent variables, respectively. To control for multiplicity, analysis of primary and secondary endpoints will be carried out using a hierarchical testing approach with the following sequence: PAID, HbA1c, DSMQ, DES, percentage of hypoglycemic blood glucose values, number of blood glucose measurements per day, percentages of euglycemic and hyperglycemic values, average blood glucose levels, GSE, WHO-5, and DSat. For statistical analysis, SPSS 25 and Systat 12 will be used. All data will be treated confidentially and stored in pseudoanonymized form, anonymized when possible, and deleted after the end of the study. [name] will have access to the final trial dataset and will be responsible for analyses.

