## Discussion

In this article, we present the study design of a multicenter, open-label, randomized, parallel-group, controlled trial to evaluate the health care effects and medical benefits of a smartphone-based diabetes self-management app. Outcome measures will comprise both direct medical benefits on blood glucose levels, HbA1c, and quality of life as well as patient-reported outcomes relevant for the health behavior of people with diabetes such as treatment adherence, patient autonomy, and coping with illness-related difficulties in everyday life.

We decided to initiate a prospective randomized, controlled study to potentially prove the causation of benefits and effects and to enhance evidence by randomization of patients and intention-to-treat analyses [41]. This study is intended to confirm the findings of a retrospective systematic analysis of 5920 mySugr PRO users (57.8% people with type 2 diabetes), as required by the Digital Healthcare Act. In this study, the largest group (*n* = 3836, initial eHbA1c < 7.5%) showed a stable eHbA1c of around 6.4% over 3 and 6 months. In the subgroup with initial eHbA1c > 9%, eHbA1c levels decreased by 1.5% and 1.7% after 3 and 6 months, respectively [27]. Since HbA1c analysis is generally accepted to provide evidence on the average blood glucose level during the previous 8 to 12 weeks [42], we concluded that the 12-week duration of the study period should be sufficient to demonstrate effectiveness. Furthermore, the criteria of the Digital Healthcare Act require the final study report to be completed within 12 months after the beginning of recruitment [26]. A longer follow-up period would therefore not be feasible. Likewise, the choice of the control group (treatment-as-usual) seems to be appropriate because no other digital application for diabetes self-management has been assessed in an approach meeting comparable scientific and methodological requirements so far.

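### The visit-2 HbA1c, second in the testing sequence, need not be sampled near week 12, so early or pre-allocation values can count as the outcome

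*Protocol article*

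**What the plan says.** In the protocol article, Procedures lists the blood glucose data gathered at visit 1. Average glucose and the percentages by range are self-monitored values. HbA1c is described differently: "as well as the last documented or routinely assessed HbA1c". The same section then states that "Follow-up examination at visit 2 will assess the same data as the baseline evaluation at visit 1", extended by questionnaires for the app group. There are only two visits: "our study will comprise a 12-week study period that starts and ends with study visits for baseline and follow-up examinations". The article mentions no HbA1c draw at visit 2, no earliest permitted date and no window.

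The Discussion supports the 12-week duration by saying that HbA1c is accepted to "provide evidence on the average blood glucose level during the previous 8 to 12 weeks".

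Statistical analysis compares the arms by "analysis of covariance with baseline data as a covariate", replaces missing values by multiple imputation, and controls multiplicity by a "hierarchical testing approach with the following sequence: PAID, HbA1c, DSMQ, DES", followed by the glucose metrics, GSE, WHO-5 and DSat. Glycemic control is the second of the three hypotheses listed under Study design.

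**The concern.** Read together, the two sentences in Procedures allow the follow-up HbA1c to be whatever value is latest on file when the participant attends visit 2. That may be a routine sample from week 3 or week 5. If no test was done after allocation, it may be the baseline value entered a second time. Such a value reflects, wholly or mostly, glucose from before the app was used. The Discussion's argument for 12 weeks works only if the sample is taken at or near week 12.

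The planned handling of missing data does not help, because an old value is present and is not missing.

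Three things are at stake:
- The estimated HbA1c effect shrinks if old values are equally common in both arms.
- It is biased in an unknown direction if they are not. The trial is open label, so centres could obtain fresh values more often in one arm.
- HbA1c comes directly after PAID in the sequence. Missing significance there ends confirmatory testing of the nine listed items that follow, from DSMQ to DSat.

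**Working it through.** **The plan's own figure.** Study population sizes the trial on PAID with an "expected effect size of 0.3 standard deviations", 2:1 allocation, two-sided alpha 0.05 and power 0.80. With 132 and 264 participants the noncentral t calculation gives power 0.8016, so 396 is reproduced. Then 396/0.85 = 465.9, so 466 is reproduced. These figures are not in dispute. The article gives no effect size, SD or power for HbA1c.

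**Share of the effect that an early sample captures.** Inputs: the look-back L of 8 to 12 weeks (Discussion), and two assumptions that are not in the document, namely a constant effect on glucose from day 0 and a known weighting of past weeks. For a sample at week t, with t < L:
- flat weighting: c(t) = t/L
- linear weighting towards recent weeks: c(t) = 1 − (1 − t/L)²
- for t ≥ L, c(t) = 1; for a sample drawn before allocation, c = 0

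| Sample | L = 12 (flat, recency) | L = 8 (flat, recency) |
|---|---|---|
| Week 4 | 33%, 56% | 50%, 75% |
| Week 6 | 50%, 75% | 75%, 94% |
| Week 12 | 100%, 100% | 100%, 100% |

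**Average over sampling times uniform on weeks 0 to 12** (a further assumption):
- L = 12, flat: (1/12) × 6 = 0.50
- L = 12, recency: (1/12) × (12 − 12/3) = 0.67
- L = 8, flat: (1/12) × (4 + 4) = 0.67
- L = 8, recency: (1/12) × (8 − 8/3 + 4) = 0.78

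**What that could do to power.** Assume, only for illustration, a true HbA1c effect of 0.3 SD. With 132 and 264 participants, SE = √(1/132 + 1/264) = 0.1066 SD, and power ≈ Φ(0.3c/0.1066 − 1.96), where c is the captured share:
- c = 1: 80%
- c = 0.78: 59%
- c = 0.67: 47%
- c = 0.50: 29%

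**Pre-allocation values.** If a share f of follow-up values carries no treatment effect, equally in both arms, the expected difference is (1 − f) times the true one. A simulation of the planned ANCOVA (4000 runs per setting, baseline correlation 0.5 and 0.7, effect scaled to 80% power without old values) gave these powers:
- f = 20%: about 60 to 61% if the old value is a separate pre-exposure measurement, and 67 to 69% if it is the baseline value reused
- f = 50%: about 29% and 44 to 47% respectively

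Reusing the baseline costs less power because it also lowers the residual variance, but the estimate is diluted just as much. At correlation 0.5 it fell from 0.26 to 0.21 (f = 20%) and 0.13 (f = 50%) in both cases.

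**An old baseline value is a different problem.** A covariate measured before allocation is independent of the randomised arm. If it is out of date it correlates less with the outcome and the ANCOVA loses precision, but the estimated group difference is not pulled towards zero.

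**The case against.** The strongest reply is that the article does not say old values will be used. The HbA1c phrase stands in the account of visit 1, and the follow-up sentence may mean the same variables and not the same way of obtaining them. A routine assessment may well be done at the centre on the day of visit 2, and the Discussion's look-back argument suggests that a value near week 12 was intended. The article also condenses a fuller Clinical Investigation Plan, which may set a window and already collect dates.

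This stands as far as certainty goes: dilution is possible, not shown. It does not remove the point, because the wording the article does give admits a pre-allocation value as the outcome.

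A reader might go further and infer that the HbA1c test is likely to fail because of this. The document does not support that. It gives no expected HbA1c effect, and the power figures above borrow 0.3 SD from PAID. In the retrospective analysis cited in the Discussion, the largest group (3836 of 5920 users) had a stable estimated HbA1c, so the test could miss significance even with perfect timing. Equal dilution in both arms is also conservative for a superiority claim, and unequal timing between arms is a risk, not an observed fact.

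**Conclusion.** The point holds as a weakness in a stated measurement rule. The follow-up HbA1c is not tied to week 12, which conflicts with the article's own reason for a 12-week study, and multiple imputation would not catch the affected values.

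Its size cannot be derived from the document, since the age and share of old values and the HbA1c effect are not given. Under the assumptions shown, the captured effect ranges from 50 to 67% (12-week look-back) to 67 to 78% (8-week look-back), and it is 100% if every centre samples at visit 2. The primary PAID analysis is untouched. The consequence falls on HbA1c and, through the hierarchy, on the confirmatory status of what follows. This should be fixed, but it does not threaten the trial's main result: it concerns a secondary endpoint, and how often it would occur is unknown.

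**What to change.** - Record the sampling date of every HbA1c.
- Define the visit-2 HbA1c as one sampled at visit 2 or within a pre-specified window around it (for example ±14 days), and never before allocation.
- Set a matching window before allocation for the baseline value, to protect precision.
- Treat follow-up values outside the window as missing under the planned multiple imputation.
- Report the distribution of sampling dates by arm, so that differential timing can be seen.

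If the Clinical Investigation Plan already contains these rules, a sentence in Procedures stating them is enough. Otherwise the cost is a date field and a few lines of text, plus laboratory tests where centres would not have sampled at visit 2. The main downside is that more HbA1c values become missing and are imputed. Sampling at visit 2 keeps that number small; relying on the window alone could leave a sizeable part of the endpoint imputed if old values are common.

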**Fig. 1 Fig1:**
[figure not shown]
Study visits and procedures. At baseline and follow-up examination, blood glucose data will be collected, and questionnaires on patient-reported outcomes will be completed by all participants. Participants of the interventional group will further report their real-world experience with mySugr PRO by using an application for mobile ecological momentary assessments (mEMA) and by completing an additional questionnaire on the perceived quality of mySugr PRO at visit 2

### Patient-reported outcomes

At visits 1 and 2, all participants will complete the following PRO questionnaires. As the primary endpoint, the Problem Areas In Diabetes (PAID) questionnaire contains 20 items on areas of diabetes-related psychosocial distress to be rated on a 5-point Likert scale [33]. As secondary endpoints, questionnaires on diabetes self-management, diabetes-specific empowerment, general well-being, self-efficacy expectation, and treatment satisfaction will be completed at visits 1 and 2. In detail, the Diabetes Self-Management Questionnaire (DSMQ) presents a 16-item self-report scale on glucose management, dietary control, physical activity, and health care use, with each item to be rated on a Likert scale ranging from 0 (does not apply) to 3 (very much applies) [34]. The questionnaire on diabetes-specific empowerment bases on the German version of the diabetes empowerment scale (DES; 11 items to be rated on a 4-point scale; [35]). General well-being will be assessed by the WHO-5 scale, in which patients will be required to rate how well each of five statements applies when considering the last 14 days [36]. The questionnaire on general self-efficacy (GSE) contains 10 items to be rated on a 4-point Likert scale [37]. For the evaluation of diabetes treatment satisfaction, we used the questionnaire for the assessment of diabetes-related problems and satisfaction with insulin treatment (DSat; [38]). The DSat questionnaire has 10 questions, each of which is scored on a scale ranging from 1 (very satisfied) to 6 (completely dissatisfied). The topics of this questionnaire include satisfaction with glucose levels, flexibility, and hypoglycemia. At visit 2, participants of the interventional group will additionally complete an adapted version of the Mobile Application Rating Scale (MARS) to assess the perceived quality of the intervention [39]. All primary and secondary outcomes are depicted in Fig. 2.

**Fig. 2 Fig2:**
[figure not shown]
Primary and secondary endpoints and additional measures. PAID, Problem Areas In Diabetes [33]; DSMQ, Diabetes Self-Management Questionnaire [34]; DES, Diabetes Empowerment Scale [35]; WHO-5, well-being scale [36]; GSE, general self-efficacy [37]; DSat, treatment satisfaction [38]; MARS, Mobile Application Rating Scale [39]; mEMA, mobile ecological momentary assessments

### Statistical analysis

All evaluations on positive care effects will base on intention-to-treat analyses. Missing values will be identified and replaced by using multiple imputation [40]. Additional sensitivity analysis will be performed with the per-protocol population. Descriptive data will be presented as absolute and relative frequencies (categorical, nominal data), median and interquartile range (75% percentile and 25% percentile; ordinal data), and mean ± SD (interval-scaled variables). The differences between the interventional and control groups will be assessed by the analysis of covariance with baseline data as a covariate, and follow-up data and group membership as dependent and independent variables, respectively. To control for multiplicity, analysis of primary and secondary endpoints will be carried out using a hierarchical testing approach with the following sequence: PAID, HbA1c, DSMQ, DES, percentage of hypoglycemic blood glucose values, number of blood glucose measurements per day, percentages of euglycemic and hyperglycemic values, average blood glucose levels, GSE, WHO-5, and DSat. For statistical analysis, SPSS 25 and Systat 12 will be used. All data will be treated confidentially and stored in pseudoanonymized form, anonymized when possible, and deleted after the end of the study. [name] will have access to the final trial dataset and will be responsible for analyses.

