### Randomization, sequence generation, and blinding

Randomization will be performed by a computer-generated randomization sequence (Research Randomizer [32]), assigning participants to the interventional or control group in a 2:1 ratio, by block randomization with an initial block size of six and three for subsequent participants. Study centers will receive concealed envelopes with the randomization results for each participant separately. The respective envelope will be opened by the study staff at the first study visit of the participant, and the participant will be allocated accordingly. Due to the nature of the intervention, blinding of participants and study centers providing the intervention will not be possible.

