As outcome measures, we will not only assess the direct medical effects on blood glucose and HbA1c levels because of their relationship with diabetic complications [43, 44] but also several PRO assessing psychological aspects of diabetes that have been shown to be important to people with diabetes [45, 46]. Preliminary evidence for the beneficial effects of mySugr on specific PRO was obtained in a retrospective systematic analysis, which was conducted during the application process for the Digital Healthcare Act. In this study, the comparison of 1099 study participants using the app with a historical cohort of 824 non-users revealed significantly decreased PAID-5 scores in app users with type 1 or type 2 diabetes (overall sample, 6.32 ± 4.36 vs. 5.07 ± 4.20, *t*(1921) = 6.36, *p* < 0.001; type 1 diabetes, 6.55 ± 4.30 vs. 5.12 ± 3.96, *t*(815) = 4.85, *p* < 0.001; type 2 diabetes, 6.01 ± 4.42 vs. 4.96 ± 4.23; *t*(1066) = 3.75, *p* < 0.001) [27]. Therefore, diabetes distress will be evaluated as the primary endpoint by the PAID questionnaire [33], a widely accepted scale to assess diabetes distress, since its results are associated with the functionality of coping styles, quality of life, and the occurrence of depressive symptoms [47]. Diabetes distress is common among people with diabetes, with a prevalence of approximately 20 to 40% [48, 49] and 36%, respectively [12]. Diabetes distress hinders the optimal management of diabetes and impacts on the emotional well-being, self-care, and quality of life of people with diabetes [13, 50] and, therefore, represents an important and valid outcome measure [51–53]. The broad spectrum of secondary endpoints then aims at reflecting the complexity of diabetes therapy and care that includes the self-management of dietary control, physical activity, and health care use, as well as diabetes-specific empowerment, self-efficacy, and satisfaction with current treatment. There is a great body of evidence that corresponding PRO are clinically relevant as they are associated with glycemic parameters [54], which is particularly true for PRO measures such as diabetes distress and self-management behaviors [13, 47, 50, 55].

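### Under 2:1 allocation, the plain ANCOVA gives a slightly wrong standard error if residual spread differs between arms; naming HC3 standard errors is a minor, nearly free improvement

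*Protocol article*

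**What the plan says.** The Statistical analysis section of the protocol article sets one model for all group comparisons: "The differences between the interventional and control groups will be assessed by the analysis of covariance with baseline data as a covariate", with "follow-up data and group membership as dependent and independent variables, respectively". It lists no other model term and does not name the standard error. The same section runs the primary and secondary endpoints through a fixed sequence from PAID to DSat, after multiple imputation of missing values.

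The section on randomization fixes unequal arms, "assigning participants to the interventional or control group in a 2:1 ratio". The sample size under Study population rests on "the assumption of an expected effect size of 0.3 standard deviations", that is, one SD for both arms, "with a two-sided *α* error of 0.05".

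The Discussion gives the only arm-wise spreads in the article. They are PAID-5 scores from a retrospective comparison of 1099 app users with 824 historical non-users. In type 1 diabetes, for example, the values are "6.55 ± 4.30 vs. 5.12 ± 3.96". Since the text reports lower scores in users, the first figure of each pair belongs to non-users.

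**The concern.** An analysis of covariance with no stated variance estimator is by default the ordinary one, which assumes the same residual variance in both arms. With equal arms a breach of that assumption largely cancels out. With 2:1 arms it does not. The pooled variance is weighted 2:1 towards the larger app arm, while the variance of the group difference is driven 2:1 by the smaller control arm. A larger trial does not cure this, because the ratio of the two does not depend on sample size.

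If the app narrows the spread of an outcome, the ordinary test rejects slightly too often and its interval is slightly too short. If the app widens the spread, power is lost. PAID is the first test in the sequence, so its standard error affects whether any later endpoint is reached.

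**Working it through.** **Inputs from the article.** Allocation 2:1; two-sided alpha 0.05; effect 0.3 SD; power 0.80; 396 evaluable, which is 264 app and 132 control; 15% drop-out; 466 recruited. PAID-5 SDs, non-users and users: 4.36 and 4.20 overall, 4.30 and 3.96 in type 1, 4.42 and 4.23 in type 2.

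**Assumptions.** The article does not give the residual SD ratio in this trial; 0.8 to 1.25 (control to app) is taken as a range. The simulations use a baseline slope of 0.6.

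**Step 1: the plan's own figure.** The article reports that "power analysis revealed that 396 participants would be required to achieve a power of" 0.80. The normal approximation gives a control arm of 1.5 × (1.960 + 0.842)² / 0.3² = 1.5 × 7.849 / 0.09 = 130.8, so 131 control and 262 app, 393 in all. The t-based calculation gives power 0.7996 at 395 and 0.8026 at 398, which fits 396. Then 396 / 0.85 = 465.9, so 466. The figure is reproduced, with one SD for both arms.

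**Step 2: ordinary against true variance.** Let Va and Vc be the residual variances in the app and control arms, and n the control arm size, so the app arm is 2n.

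- Ordinary SE² = [(2Va + Vc)/3] × (1/(2n) + 1/n) = (2Va + Vc)/(2n)
- True SE² = Va/(2n) + Vc/n = (Va + 2Vc)/(2n)

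With r the control-to-app SD ratio, k² = ordinary SE² / true SE² = (2 + r²)/(1 + 2r²). The true size of the test of equal means is 2Φ(−1.96k). With equal arms the two variances coincide and k = 1.

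**Step 3: numbers.**

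| r (control/app) | Source | k | True size | Coverage of 95% CI |
|---|---|---|---|---|
| 4.36/4.20 = 1.038 | article, overall | 0.988 | 5.3% | 94.7% |
| 4.42/4.23 = 1.045 | article, type 2 | 0.985 | 5.3% | 94.7% |
| 4.30/3.96 = 1.086 | article, type 1 | 0.973 | 5.7% | 94.3% |
| 1.00 | equal spread | 1.000 | 5.0% | 95.0% |
| 1.20 | assumed | 0.942 | 6.5% | 93.5% |
| 1.25 | assumed | 0.929 | 6.9% | 93.1% |
| 0.80 | assumed | 1.076 | 3.5% | 96.5% |

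**Step 4: simulation of the ANCOVA** (20,000 to 30,000 trials per row, no mean effect, equal slopes).

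| r | Arms (app/control) | Ordinary SE | HC3 SE |
|---|---|---|---|
| 1.00 | 264/132 | 5.0% | 4.9% |
| 1.038 | 264/132 | 5.3% | 4.9% |
| 1.086 | 264/132 | 5.5% | 4.7% |
| 1.086 | 311/155 | 5.9% | 5.1% |
| 1.25 | 264/132 | 6.8% | 4.9% |
| 0.80 | 264/132 | 3.4% | 4.8% |
| 1.25 | 198/198 | 5.1% | 5.0% |

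The simulation agrees with the formula, and the last row shows that the problem comes from the unequal allocation.

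**Step 5: power at 264/132**, unadjusted as in the design, effect 0.3 control SDs. Equal spread: 0.804 with either standard error. At r = 0.8: 0.682 ordinary, 0.733 robust. At r = 1.25: 0.881 ordinary, 0.851 robust; part of the ordinary test's advantage there comes from its inflated size.

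**Step 6: how firm are the article's SDs?** For the overall sample, F = (4.36/4.20)² = 1.078 on 823 and 1098 degrees of freedom, p = 0.25. This is compatible with equal variances.

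**The case against.** The strongest reply is that baseline-adjusted ANCOVA is a standard prespecified analysis, and that the variance estimator is a detail an article commonly leaves to the full protocol or analysis plan, neither of which is shown. The article does not exclude robust standard errors. This stands: silence on the estimator is not a defect in itself. What remains is that the article does name the model and the 2:1 ratio, and that a better-protected version of the same analysis is available.

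The evidence for unequal spread is also weak, and this too stands. The SDs are for PAID-5, whereas the trial uses the 20-item PAID. They come from a non-randomised historical comparison. They are raw SDs, while ANCOVA depends on residual SDs after baseline adjustment. The type 1 and type 2 comparisons largely repeat the overall sample, so the three are not independent confirmations.

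A reader might infer from the eHbA1c results that the app's effect depends on baseline, so that a group-by-baseline term is needed. The article reports that values were stable below 7.5%, and "In the subgroup with initial eHbA1c > 9%, eHbA1c levels decreased by 1.5% and 1.7% after 3 and 6 months". Those are app users only, grouped by their initial value. Without a control arm the pattern cannot be told apart from regression to the mean, which the baseline covariate already absorbs. Nor would unequal slopes matter much: with equal residual SDs they moved the simulated size only to about 5.2%. Adding the interaction to HC3 gave about 6.0% in a run with a large slope difference, against 5.0% for HC3 alone. The interaction is therefore not recommended.

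**Conclusion.** The point holds as a minor improvement. Under 2:1 allocation, the ordinary ANCOVA standard error is inconsistent if residual spread differs between arms. At the SD ratios in the article, the true size would be 5.3% to 5.7% in place of 5%, with interval coverage of 94.3% to 94.7%. This takes raw PAID-5 SDs as a stand-in for residual SDs in this trial. Sizes of 6.5% or 3.5% need assumed ratios of 1.2 or 0.8, which the article does not give.

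A reader might infer that p-values and intervals will be wrong from PAID onward. The article does not support that. The distortion is conditional on the app changing the spread, and its direction depends on which arm is more variable. If the app leaves the outcome distribution unchanged, the test is valid.

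**What to change.** Keep the ANCOVA as specified. Add one sentence to the Statistical analysis section or the analysis plan, before the data are analysed: all group comparisons use heteroscedasticity-consistent (HC3) standard errors, with estimates and variances pooled over the imputed data sets by Rubin's rules. Do not add a group-by-baseline interaction.

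The cost is that sentence and a check that the named software delivers these standard errors. No extra data or participants are needed and the sample size stands. If variances are in fact equal, the loss of precision is negligible (power 0.804 either way in the design calculation).
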